**Figure P1: Timing of Questionnaires on Testing Days**

Assessing subject (participant) and site (technician) burden through questionnaires

[figure not shown][figure not shown]

[figure not shown]

## Detailed questionnaires

### Subject burden

- Entry questionnaire Day 1, e.g previous experience
  - Have you previously participated in EEG experiments?
  - Have you previously made EEG recordings yourself?
  - Have you previously participated in neuroimaging experiments?
  - Did you have a tea/coffee today before coming?
- Entry questionnaire Day 8, e.g previous experience
  - Did you have a tea/coffee today before coming?
- Exit debrief questionnaire, e.g rank orders, comments
  - Which device would you classify as your preferred one ? And why ?
  - Which device would you classify as your less preferred ? And why ?
  - What did you observe in terms of comfort?
  - What did you observe in terms of ease of use?
- ▲ Likert scale (e.g. 6 point) or VAS for comfort ratings
  - Indicate on a scale from 1 = did not notice it at all to 7 = extremely uncomfortable
- ◆ Interim debrief for the specific device, e.g. comments on pressure discomfort, weight, agility, overall flow
  - How strongly did tactile sensations of the device attract your attention during the recording?
  - How strongly did the device feel like a foreign object?
  - How strong was your urge to remove the device from your head?

### Site burden

- Questionnaire after training, e.g previous experience, expectations
  - Years of experience in performing EEG experiments
  - Previous experience with new EEG devices (active electrodes, wireless, recording software)
  - What are your expectations?
- Questionnaire after the Dummy Runonce, e.g expectations
  - Which device would you classify as your preferred one ? And why ?
  - Which device would you classify as your less preferred ? And why ?
- Exit debrief for the experimental day, e.g rank orders, comments on pain points
  - Please order the devices according to your overall preference from 1 = best device to 4 = worst device
  - What did you observe in terms of set up
  - What did you observe in terms of clean up
  - What did you observe in term sof recordings?
- Exit debrief questionnaire for the study e.g best and worse devide, comments
  - Which device would you classify as your preferred one ? And why ?
  - Which device would you classify as your less preferred ? And why ?
- ◆ Interim debrief clean-up, e.g. ease of cleaning, clean up time, comments (Likert scale?)
  - Indicate on a scale from 1 = very easy to clean up to 7 = extremely difficult to cleanup

## **LIST OF ABBREVIATIONS**

|         |                                           |
|---------|-------------------------------------------|
| AASP    | Adolescent/Adult Sensory Profile          |
| ANOVA   | Analysis of Variance                      |
| CRO     | Contract Research Organization            |
| CV      | Coefficient of Variation                  |
| D       | Day                                       |
| EEG     | Electroencephalogram                      |
| EOG     | Electrooculogram                          |
| ERP     | Event-related-potential                   |
| ET      | Eye tracking                              |
| FU      | Follow-up visit                           |
| HEOG    | Horizontal EOG                            |
| HEOGL   | Left HEOG                                 |
| HEOGR   | Right HEOG                                |
| ICF     | Informed Consent Form                     |
| ICH     | International Conference on Harmonization |
| IEC     | Independent Ethics Committee              |
| SOA     | Schedule Of Activities                    |
| VEOG    | Vertical EOG                              |
| VEOGL   | Upper VEOG                                |
| VEOGU   | Lower VEOG                                |
| WHODRUG | World Health Organization Drug Dictionary |
| WMA     | World Medical Association                 |

### 3. **INTRODUCTION**

Electroencephalogram (EEG) assessments in clinical trials are performed using non-invasive scalp electrodes. These electrodes require the application of a highly conductive electrolytic EEG gel between the scalp and the electrode to obtain good contact and reduce the impedance of the skin-electrode interface. Preparing the wet EEG cap is a time-consuming procedure that can be burdensome for patients.

New EEG recording devices that use dry or semi-dry electrodes may substantially reduce the set up time and burden for patients and clinical sites, however their signal quality and comparability to the current standard are unclear.

The main objective of this study is to compare the quantitative performance in terms of signal quality of three EEG recording devices, their ease-of-use through clinical sites and study participant's comfort, versus the standard set-up of a wet EEG cap.

The objective of the study is not to perform any absolute assessment of the performance of the devices (each device has already been certified and is considered as fully functional). The purpose of this project is to compare each tested device to a reference EEG system.

#### 4. OBJECTIVES AND ENDPOINTS

|                  | Objective                                                                                                                               | Endpoint                                                                                                                                                                                                                                                                                                                                                                                                                                                                                                                                          |
|------------------|-----------------------------------------------------------------------------------------------------------------------------------------|---------------------------------------------------------------------------------------------------------------------------------------------------------------------------------------------------------------------------------------------------------------------------------------------------------------------------------------------------------------------------------------------------------------------------------------------------------------------------------------------------------------------------------------------------|
| Primary   | To compare the quantitative performance in terms of signal quality between three new EEG systems and a standard clinical wet EEG system | 
 
- EEG features derived from resting state recordings
 
- Latencies and amplitudes of evoked components as well as Signal-to-Noise Ratio from an auditory oddball task
 
- Visual gamma activity (e.g. power and peak frequency)
 
- Test-retest reliability of all EEG derived features during resting state and task recordings
 
- Robustness to artefacts and non-neural signal sources
 
                                                                          |
| Secondary | To compare the participant burden between three new EEG systems and a standard clinical EEG system                                      | 
 
- Subjective comfort assessed at multiple time points during a recording session
 
- Interim debrief obtained after recording with each device for detailed feedback on each device
 
- Exit debrief at the end of a recording day including a subjective rank ordering of devices from best to worst
 
- Exit debrief at the end of the study including a subjective rank ordering of devices for the best and the worse one as well as some explanation of the selection
 
 |
| Secondary | To compare the site (Technician) burden between three new EEG systems and a standard clinical EEG system                                | 
 
- Set-up (from installation of the system to start of the recording) and clean-up timings for each EEG device
 
- Interim debriefs on ease of clean up
 
- Exit debrief at the end of a recording day including a subjective rank ordering of devices for the best and the worse one
 
- Exit debrief at the end of the study including a subjective rank ordering of devices for the best and the worse one as well as some explanation of the selection
 
                  |

## **5. STUDY DESIGN**

### **5.1. Overall Design**

This is a study that will be performed at a single center involving neurotypical female and male participants.

The study will consist of two assessment visits per participant the clinical site (initial test sessions at D1 Visit 1 followed by re-test sessions at D8 Visit 2, approximately one week later). The participant will have been informed of study specific lifestyle restriction by a phone call before attending the first visit.

The staff will have to follow a training session on the full equipment including dummy runs followed by a post-training questionnaire before the first visit.

At each assessment visit, each participant will be subjected to EEG recordings using the 4 devices (test device 1, test device 2, test device 3 and the reference wet EEG cap) and each test session will consist of the recording of a resting state EEG followed by an auditory oddball task (P300), by a visually evoked potential test (specifically targeting activity in the  $\gamma$  band), a controlled artefact stimulation test (investigating the sensitivity of the systems to a series of standardized actions known to generate EEG interferences). All questionnaires will be completed after each test session, before the participant can proceed to the next session.

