| Design: 
This study will be performed at a single center, in a Phase 1 unit and involve neurotypical female and male participants. The experimental environment is intended to mimic closely the conditions of a clinical trial, in order to allow for the identification of the ideal EEG system for future clinical trials.
 
The study will consist of two assessment visits per participant at the clinical site (initial test sessions at D1 Visit 1 followed by re-test sessions at D8 Visit 2, approximately one week later).
 
The participants will be informed of study specific lifestyle restrictions in a phone call before the first visit.
 
The staff will be trained on the study conduct, including dummy runs, before the first visit of the first participant.
 
At each assessment visit, each participant will perform EEG recordings using the 4 devices (test device 1, test device 2, test device 3 and the reference wet EEG cap) and each device session will consist of 4 separate EEG recording types: resting state, auditory oddball task (P300), visually stimulation (specifically targeting activity in the <math>\gamma</math> band), a controlled artefact session (investigating the sensitivity of the systems to a series of standardized actions known to generate EEG interferences). Ease-of-use and comfort questionnaires will be completed after each test session by the participant as well as the technician.
 
The sequence of EEG devices recorded within each participant will be randomized according to a Latin square design, and consecutive EEG recordings will be separated by half an hour.
 
The same order of EEG devices will be applied to both visits of each participant to minimize within participant variability.
 |                                                                                                          |                                                                                                                                                                                                                                                                                                                                                                                                                                                                                                                             |                          |                                                                                            |                       |                                                                                                   |                       |                                                                                                  |                       |                                                                                                  |

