| Urine Drug Screen                                                                                                                  |                              | X                       |                               | X                |
| Randomization                                                                                                                      |                              |                         | X [a]              |                  |
| 4 test sessions [c] : resting state EEG, ERP tests (auditory and visual task), and controlled artefact stimulation test |                              |                         | X                             | X                |
| Participant's questionnaires [e]                                                                                        |                              |                         | X                             | X                |
| Clinical staff questionnaires [f] [g]                                                                                   |                              |                         | X                             | X                |

[a] Randomization;

[b] The participants will be asked if they maintained a stable lifestyle before inclusion (physical activity, hours of sleep).

[c] The device assessment visit consists of 4 sessions, one per device. Each session lasts approximately 1 hour and consists of a resting state EEG, ERP tests (auditory oddball and visual ERP), and controlled artefact stimulation test; The order for performing the tasks will be the same for all devices.

[d] The participant's questionnaires will comprise an entry questionnaire, an exit questionnaire (for D1 Visit 1 and D8 Visit 2) and three interim questionnaires: one performed before, between and after (for comfort rating) each task for each device and a third one after a device has been tested and before the next device is set up. A summary description of the timing of questionnaires is provided in [Figure P1](#).

[e] The clinical staff's questionnaires will comprise an entry questionnaire (for D1 Visit 1 only), an exit questionnaire and two interim questionnaires (one for rating the system set-up, and a second one rating device cleaning). A summary description of the timing of questionnaires is provided in [Figure P1](#).

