## **10.5. Questionnaires and timing data**

### **10.5.1. Outcome measurements**

**All questionnaires are provided in Appendix 3 and an overview of the schedule of assessments for the questionnaires is provided in Figure P1.**

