#### **Participant's questionnaires:**

- Entry questionnaire answers;
- Interim-before assessment questionnaire answers;
- Interim-after assessment questionnaire answers;
- Interim-after task questionnaire answers;
- Exit questionnaire answers.

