| 
Exit debrief questionnaire
 [figure not shown] 
System ranking
 | 
Rules (on screen) = Please answer to the next 4 questions, your answers will be used to define your preference list of the systems.
 
 
● Please rank the devices in order of preferences.
 
○ Device #1
 
○ Device #2
 
○ Device #3
 
○ Standard EEG Device
 
● Why did you choose your preferred device as the best one?
 
● Why did you choose your less preferred device as the worst?
 
● Are you looking forward to performing the second session? (Day 1 only) and why (free comments)?
 
○ YES
 
○ NO
 
● Anything to add? (free comments)
 
 |
| 
After each task
 [figure not shown] 
VAS Comfort
             | 
Is the equipment currently uncomfortable to wear?
 
Very uncomfortable Do not notice the device at all
 [figure not shown]                                                                                                                                                                                                                                                                                                                                                                                                                              |
| 
Interim debrief
                                                                                                                    |                                                                                                                                                                                                                                                                                                                                                                                                                                                                                                                                                                                                                                                                               |

|                                                                                   |                                                                                                                                           |

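### Section 5.1 and the synopsis Design time the comfort questionnaires after each session, which contradicts the in-session comfort endpoint, SoA footnote [d] and the Appendix 3 comfort VAS

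*Protocol*

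**What the plan says.** The endpoint appears in the synopsis and in Section 4: "Subjective comfort assessed at multiple time points during a recording session". It is listed first under participant burden, a secondary objective.

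The timing of the questionnaires is described in several places:

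- **Section 5.1:** "All questionnaires will be completed after each test session, before the participant can proceed to the next session".
- **Synopsis, Design:** "Ease-of-use and comfort questionnaires will be completed after each test session by the participant as well as the technician".
- **Section 2, SoA footnote [d]:** among the interim participant forms, "one performed before, between and after (for comfort rating) each task for each device". The footnote refers to Figure P1 for a summary of timing.
- **Section 10.5.1:** "All questionnaires are provided in Appendix 3", with Figure P1 again named for the schedule. The participant outcomes listed there include "Interim-before assessment questionnaire answers", separately from an after-task form.
- **Appendix 3, Participant Burden:** the comfort VAS sits in a row headed "After each task" and asks "Is the equipment currently uncomfortable to wear".

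**The concern.** A session, as the synopsis and Section 5.1 describe it, contains all four recordings made with one device. A questionnaire completed after the session is therefore completed once per device, when the recordings are over. One such rating is not a set of ratings within the session, so the overview sentences describe a data collection that cannot produce the endpoint.

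The item wording sharpens the conflict. It asks about comfort at the present moment, so an answer given after the session cannot stand in for the ratings that should have been made between tasks.

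This concerns data collection and cannot be left to the analysis. A comfort rating not taken during the session cannot be recovered later.

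**Working it through.** The protocol states no figure for the number of comfort ratings, so there is nothing to reproduce. The check compares the timing statements and counts the ratings each implies.

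**Inputs**

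- Participants: 32 (Section 5.2).
- Devices, one session each per visit: 4 (SoA footnote [c]).
- Visits: 2 (Section 5.1).
- Tasks per session: 4 (synopsis Design; Section 10.4.1), with eyes-open and eyes-closed resting state counted as one task.

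**Device sessions**

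participants × devices × visits = 32 × 4 × 2 = 256.

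**Comfort ratings implied by each statement, with complete data**

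| Source | Ratings per session | Total | Several ratings within the session? |
|---|---|---|---|
| Section 5.1 and synopsis Design, read literally | 1 | 1 × 256 = 256 | No |
| Appendix 3 row heading | 4 (one after each task) | 4 × 256 = 1,024 | Yes |
| SoA footnote [d], one reading | 5 (one before the first task, three between tasks, one after the last) | 5 × 256 = 1,280 | Yes |

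The footnote can be parsed in more than one way, so five is the count on one reasonable reading.

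**Worst-case shortfall under the literal overview sentences**

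- Against Appendix 3: 1 − 256/1,024 = 75%.
- Against footnote [d] as read above: 1 − 256/1,280 = 80%.

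**Which statements conflict with the endpoint**

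Only Section 5.1 and the synopsis Design do. Four after-task ratings already amount to several time points within a session. Appendix 3 therefore satisfies the endpoint, and its times fall within those of footnote [d]. The remaining difference between Appendix 3 and footnote [d] is the rating before the first task, which the footnote and the Section 10.5.1 list call for and the Appendix 3 heading does not mention.

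**The case against.** The best defence is that the two sentences are overview text and the detailed schedule is sound. In Section 5.1 the word for all questionnaires cannot be literal: the same section places a staff questionnaire after training, and the entry and exit forms are not tied to a session. Its last clause can be read as a deadline, meaning that the forms must be finished before the next device starts. The synopsis sentence covers both participant and technician, which fits the post-device debriefs at least as well as the task-level VAS.

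This explains how the wording may have arisen but does not remove the conflict. The deadline reading strains the words of Section 5.1. It is not available for the synopsis, which names comfort and has no such clause.

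Three stronger conclusions might be inferred, and the documents do not support them.

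- **That comfort straight after fitting is never recorded.** Section 10.5.1 assigns the forms to Appendix 3 but the timing to Figure P1, which is not shown and may depict a rating before the first task. Footnote [d] and the Section 10.5.1 list both call for one, and the one-line VAS could simply be reused.
- **That most of the comfort data will be lost, with none taken during wear.** This requires the site to follow the overview sentences and disregard the endpoint, footnote [d], the Section 10.5.1 list and the Appendix 3 heading. Nor does the protocol say that the device is already off when the post-session forms are filled in.
- **That the study sets out to measure discomfort building up with wear time.** The endpoint asks for several time points. It does not define a baseline at fitting or a change over time, and the protocol says nothing about how discomfort develops with dry or gel electrodes.

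**Conclusion.** The contradiction is real and confined to two sentences. As written, Section 5.1 and the synopsis Design cannot deliver the comfort endpoint, and they conflict with footnote [d] and Appendix 3. Taken literally they give 256 ratings, one per device session, where 1,024 or about 1,280 are intended.

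Those counts assume 32 participants with complete data and resting state as a single task; the largest also depends on how footnote [d] is parsed. They bound the loss if the wrong sentence is followed and do not predict it. The endpoint is secondary, but the correction is worth making before the first visit because the ratings cannot be reconstructed afterwards.

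The missing mention of a pre-task rating in Appendix 3 is a lesser point, conditional on what Figure P1 shows.

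**What to change.** 1. In Section 5.1 and the synopsis Design, restrict the sentence on completion after each session to the post-device interim debrief and the staff forms. Add that the comfort VAS is completed during the session, with the device on, at the times given in SoA footnote [d].
2. Check Figure P1. If it shows a rating before the first task, or is silent, extend the Appendix 3 row heading so that the same comfort VAS is also completed before the first task. This brings the form into line with footnote [d] and the before-assessment questionnaire listed in Section 10.5.1. If the figure shows otherwise, reconcile it with those two places.

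The cost is a rewording of two sentences and possibly one form heading. Relative to Appendix 3, the second step adds one VAS mark per session and no visit or procedure.
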